### Sample Size

3.4

Table 1 summarizes the sample size for each phase and is determined based on previous effect estimates (Phase 1), the number of fixed‐effect factors to be considered in the regression model (Phases 2 and 3), and the recommended minimum sample size per treatment arm for feasibility studies (Phase 4, Table 2).

#### Phase 1

3.4.1

The sample size is calculated, considering an effect estimate (Cohen's d) of 0.78 from Wong and Kern (2011) on the sweetness taste perception obtained before and after taking MB using G*power software version 3.2, considering 80% power, α level of error of 0.05, and 20% dropout. Using paired sample *t*‐tests, 54 participants (18 in each group) will be recruited.

#### Phases 2 and 3

3.4.2

Determining sample size for mixed models (LMM/GLMM) is challenging, as statistical power depends on multiple factors, including the number of participants, repeated measures per subject, intra‐class correlation (ICC), outcome distribution, and the specified random‐effects structure (Kumle et al. 2021). Given uncertainties, particularly regarding predictors that will ultimately be retained as fixed effects in the final model, the sample size for this study is determined using an empirically informed approach. Consistent with Green (1991) guidelines for regression analyses, for behavioral research with expected large effect estimates, a minimum of 10 participants per predictor variable will be required for included to ensure model stability. In the planned mixed model, treatment (i.e., dose) will be specified as the primary fixed effect, time (pre‐post assessment) as the within‐subject factor, and participant as a random effect. Covariates such as age, sex, and phenylthiocarbamide (PTC) sensitivity will be considered for inclusion to control for potential confounding but will only be retained in the final model if they contribute meaningfully to model stability and fit. Based on an anticipated inclusion of four fixed factors in the final model, a minimum of 40 participants will be recruited for each study phase.

#### Phase 4

3.4.3

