### Data Collection Tools

3.6

Table 3 describes measurement tools for each key outcome variable and covariates in each project phase.

**TABLE 3 fsn371640-tbl-0003:** Measurement tools and their description for key variables in each phase of the project.

Phases	Variable to be measured		Tool	Description	References
Phase 1	Sour, bitter, tart and sweet taste perceptions of individual food‐based solutions and food items		Generalized Labeled Magnitude Scale (gLMS)	Ranges from 0 (barely detectable) to 100 (the strongest sensation of any kind). Participants will establish these boundaries (no sensation to strongest imaginable) before rating items	Green et al. (1996)
Phases 2 and 3	Overall liking of hypo‐palatable mixed vegetarian salad and hyper‐palatable SSB		Labeled Affective Magnitude Scale (LAMS)	Ranges from 0 (greatest imaginable dislike) to +100 (greatest imaginable like). Study participants will be asked, “How much do you like/dislike this food item? (please put a slash (/) mark somewhere on the line).”	Schutz and Cardello (2001)
	Sourness and bitterness taste perceptions of hypo‐palatable mixed vegetarian salad and sweetness taste perceptions of hyper‐palatable SSBs		Generalized Labeled Magnitude Scale (gLMS)	Ranges from 0 (barely detectable) to 100 (the strongest sensation of any kind). Before rating items, participants will establish these boundaries (no sensation to the strongest imaginable)	Green et al. (1996)
	Intake of the hypo‐palatable mixed vegetarian salad		The difference between the amount served and the amount left over	At both the pre‐test and post‐test sessions, participants will be provided with a fixed portion of mixed salad weighing 117 g, which corresponded approximately to half a serve of vegetables and half a serve of fruit according to the Australian Dietary Guidelines. Participants will be instructed to consume as much of the provided salad as they desired. Each portion will be weighed prior to serving, and any leftovers will be weighed immediately after consumption. Actual intake will be calculated as the difference between the amount served and the amount remaining	National Health and Medical Research Council (2013)

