**FIGURE 1 fsn371640-fig-0001:**
[figure not shown]
Phase 1 study design.

After the pre‐test, participants will drink water to neutralize their mouths. Group A will receive 175 mg (half a tablet), Group B will receive 350 mg (one tablet), and Group C will receive 700 mg (two tablets) doses in MB tablets. Subjects will be instructed to dissolve the tablet with saliva on their tongue for 5 min and make contact with the tablet against as much surface area of the oral cavity as possible without chewing or swallowing it (Hudson et al. 2018). Immediately after dissolving, participants will receive the same solutions and food items used for the pre‐test to capture changes in perceived taste perception on gLMS.

#### Phase 2

3.7.3

A hypo‐palatable vegetarian salad containing half‐serve vegetables (raw broccoli and rocket leaves) and half‐serve fruits (Granny Smith apple), which are the minimum possible servings per Australian dietary guidelines (Brownie et al. 2015), will be prepared 30 min before the data collection time at Griffith University, Gold Coast campus kitchen lab or the Participants' home, based on the participants' preferences. Food items for the vegetarian salad and the Coca‐Cola (representing hyper‐palatable SSB) will be purchased from the local market. The food will be stored in a refrigerator (4°C), removed, and placed on separate plastic trays 10 min before each test. The SSB will be kept at room temperature, and 30 mL will be poured into 50 mL paper cups, which are clean and uniform in color (Mielby et al. 2018).

Figure 2 shows that participants (*n* = 40) will be allocated to four treatment arms (*n* = 10 in each group). The data collection procedure will follow these steps:

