Initially, participants will review the participant information sheet and screening questions and sign a consent form. They will confirm (tick) the standardized instructions provided before their visit.Anthropometry measurements and body composition assessments will be conducted, and eligibility will be confirmed.For the TAS2R38 gene, saliva will be collected using the Oragene DNA OG‐500 kit as mentioned in Table 3.The pH of the mouth will be measured using a pH paper strip as mentioned in Table 3.Phenotypic taste sensitivity will be assessed by having participants place a PTC strip on the tip of their tongues.Rate their hunger level using the 10‐point hunger scale (0 = full, and 10 = very hungry), and assess their current mood status using a 10‐point mood scale (0 = happiness, and 10 = sadness).After rinsing their mouths with water, participants will receive a weighted vegetarian mixed salad. They will consume as much or as little from the given salad.Participants will rate the sourness and bitterness taste perception of the salad using gLMS, followed by their overall liking of the salad using the Labeled Affective Magnitude Scale (LAMS). The principal investigator will measure and record any leftover salad to measure their intake.After rinsing their mouths with water, participants will drink 30 mL of regular Coca‐Cola and rate its sweetness‐taste perception on gLMS and overall liking on LAMS.Participants will be required to wait for a compulsory 20‐min period after the pre‐testing procedures before commencing post‐testing. This interval is intended to allow hunger levels to return to baseline. The duration is based on the estimated energy content of the test meal (60 kcal, i.e., 251 kJ). Drawing on Horner et al. (2014), whose participants required approximately 3 h to recover from a ~1600 kJ meal, we calculated that ~23 min would be sufficient for our test meal; therefore, a minimum 20‐min waiting period will be adopted. As this duration may not fully account for individual differences in metabolism, dietary fiber intake, or the amount consumed during the pre‐test, participants will be verbally informed of the rationale for the interval and asked to notify the investigator once their hunger has returned to baseline. They will then be asked to complete the same hunger scale used upon arrival at the lab. If post‐waiting hunger ratings are comparable to baseline, the post‐test will proceed; otherwise, the waiting period will be extended until hunger levels return to baseline.According to their assigned group, participants will rinse their mouths and dissolve a given dose of MB (175, 350, 700 mg) or placebo (350 mg) in their mouth for 5 min.A vegetarian salad similar in content and amount to the one provided in the pre‐test will be provided. Participants will consume it as desired, and the principal investigator will measure and record any leftovers.Participants will rate the sourness and bitterness taste perception of the salad using gLMS, followed by their overall liking using LAMS.Finally, participants will rinse their mouths with water, drink 30 mL of regular Coca‐Cola, and rate the sweetness taste perception using gLMS and their overall liking using LAMS.

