2	To compare the effect of different doses of MB on sourness, and bitterness taste perceptions and overall liking of a hypo‐palatable mixed salad among healthy‐weight Australian adults	Different MB doses ○ Dose 1: ½ tablet (≈170 mg) ○ Dose 2: 1 tablet (≈350) ○ Dose 3: 2 tablets (≈700 mg) Placebo	Ratings for sourness and bitterness taste perception	gLMS (0–100)	As proposed in Phase 1 Additionally, as the sample size was determined using the empirical guideline of at least 10 subjects per predictor variable (Green 1991), and given the complexity in power estimation for mixed models, post hoc sensitivity power analysis will be conducted for planned comparisons. This will determine the minimum detectable effect size based on the achieved sample size and desired statistical power. Recent literature also recommends strengthening sample size justification for such approaches through sensitivity power analyses (Lakens 2022)
			Rating for overall liking	LAMS (0–100)	
			Intake	Served amount of salad minus left over	
	To compare the effect of different doses of MB on sweetness taste perceptions and overall liking of hyper‐palatable SSBs among healthy‐weight Australian adults	Different MB doses ○ Dose 1: ½ tablet (≈170 mg) ○ Dose 2: 1 tablet (≈350) ○ Dose 3: 2 tablets (≈700 mg) Placebo	Sweetness taste perception ratings	gLMS (0–100)	
			Ratings for overall Liking	LAMS (0–100)	
3	To compare the effect of different doses of MB on sourness and bitterness taste perceptions and overall liking of hypo‐palatable mixed salad among overweight or Obese Adults residing in Australia	Different MB doses ○ Dose 1: ½ tablet (≈170 mg) ○ Dose 2: 1 tablet (≈350) ○ Dose 3: 2 tablets (≈700 mg) Placebo	Ratings for sourness and bitterness taste perceptions	gLMS (0–100)	As proposed in Phase 2
			Ratings for overall liking	LAMS (0–100)	
	To compare the effect of different doses of MB on sweetness taste perceptions and overall liking of hyperpalatable SSBs among overweight/obese adults residing in Australia	Different MB doses ○ Dose 1: ½ tablet (≈170 mg) ○ Dose 2: 1 tablet (≈350) ○ Dose 3: 2 tablets (≈700 mg) Placebo	Ratings for sweetness taste perceptions	gLMS (0–100)	
			Ratings for overall Liking	LAMS (0–100)	

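### Salad intake in Phases 2 and 3 is capped at the 117 g served at each session, so any rise in intake from MB is under-recorded to the extent that participants finish the portion

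*Protocol article*

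**What the plan says.** Table 3 (section 3.6) fixes the test meal for Phases 2 and 3: at both sessions "participants will be provided with a fixed portion of mixed salad weighing 117 g". On how much to eat, it says "Participants will be instructed to consume as much of the provided salad as they desired". The Phase 2 procedure (section 3.7.3) agrees: at pre-test, "They will consume as much or as little from the given salad". The post-test serves "A vegetarian salad similar in content and amount to the one provided in the" pre-test. Phase 3 uses the same procedure (section 3.7.4). Nowhere is a refill or second helping offered.

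Section 3.7.3 describes the half-serve of vegetables and half-serve of fruit as servings "which are the minimum possible servings per Australian dietary guidelines", and bases the waiting time on the "estimated energy content of the test meal (60 kcal, i.e., 251 kJ").

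In Table 6 (section 3.8) the intake outcome is "Served amount of salad minus left over". It falls under the general linear or generalized mixed model set out for Phase 1. The distribution is to be chosen from the data type and diagnostics, and no censored model is named. The limitations in section 4 do not mention a ceiling.

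**The concern.** Recorded intake can only lie between 0 g and the portion served. Someone who eats x g at pre-test can gain at most 117 - x g, and someone who finishes can gain nothing but can still lose up to 117 g. The introduction argues that MB dampens sour and bitter tastes and so may raise preference for, and consumption of, such foods. The outcome is thus closed on the side where the effect is expected and open on the other.

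The placebo arm does not cancel this, because the cap removes most from the arm whose desired intake rises most. The dose comparison is the most exposed: two doses that both bring participants to the cap look alike, and a real dose-response could be read as a plateau or as no effect. Comparing doses on salad intake is a stated objective for these phases (section 2).

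**Working it through.** **The plan's own figures.** Section 3.4.2 states that "a minimum of 40 participants will be recruited for each study phase", from 10 participants per predictor and four fixed factors: 10 × 4 = 40, or 10 in each of four arms. This reproduces, but it does not rest on intake. The energy figure also reproduces: 60 × 4.184 = 251 kJ. There is no finishing rate, SD or expected effect in grams, so the rest is a range under assumptions.

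**The cap.** A pre-test finisher has a maximum recordable change of 117 - 117 = 0 g. This needs no assumption.

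**Attenuation model (assumed).** Desired intake is normal with SD s. A share p would want at least 117 g at pre-test, so the mean is μ = 117 - s·z, where z is the (1 - p) normal quantile. Arms are alike at pre-test, and MB shifts desired intake by δ at post-test. Recorded intake is desired intake clipped to 0-117 g. The mean lost at the cap for an arm with mean m is

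L(m) = s·[φ(k) - k·(1 - Φ(k))], with k = (117 - m)/s.

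Apart from the floor at 0 g, the recorded effect is δ - [L(μ + δ) - L(μ)].

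**Worked case**, p = 20%, s = 25 g, δ = 20 g:
- μ = 117 - 25 × 0.842 = 95.96 g.
- Placebo: k = 0.842, L = 25 × (0.2800 - 0.842 × 0.2000) = 2.79 g.
- MB: k = (117 - 115.96)/25 = 0.042, L = 25 × (0.3986 - 0.042 × 0.4834) = 9.46 g.
- Recorded effect = 20 - (9.46 - 2.79) = 13.33 g, which is 67% of the true 20 g.

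**Recorded effect divided by true effect**, cap and floor included, no drift (δ = 20 g / 30 g):

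| Would finish at pre-test | s = 25 g | s = 35 g | s = 50 g |
|---|---|---|---|
| 1% | 0.966 / 0.946 | 0.879 / 0.887 | 0.567 / 0.598 |
| 10% | 0.805 / 0.740 | 0.827 / 0.788 | 0.753 / 0.743 |
| 20% | 0.666 / 0.590 | 0.705 / 0.653 | 0.692 / 0.665 |
| 40% | 0.443 / 0.372 | 0.487 / 0.432 | 0.510 / 0.472 |
| 60% | 0.262 / 0.210 | 0.297 / 0.254 | 0.323 / 0.291 |

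In the 1% row the low values at the larger SDs come from the floor at 0 g. With the cap alone the ratios there are 0.95 to 0.98, so the cap costs 2-5%. The floor also contributes at 10% with s = 50 g, where the cap alone gives 0.86 / 0.83.

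**Post-test drift.** If desired intake falls by 10 g in every arm at the second salad, the ranges become 75-89% at 10%, 71-79% at 20%, 52-60% at 40% and 33-40% at 60%.

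**Dose contrast.** If two doses shift desired intake by 20 g and 40 g, the recorded 20 g difference keeps 53-70% at 10%, 36-58% at 20%, 18-36% at 40% and 8-20% at 60%.

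**Power.** A simple two-sample t test on change illustrates this: 10 per arm, two-sided 0.05, δ = 20 g, s = 25 g, assumed pre-post correlation 0.7, no drift. Power is 0.59 without a cap, and 0.49, 0.33 and 0.22 with 10%, 30% and 50% finishers.

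**The case against.** The best reply is that the cap may seldom bind. The salad (raw broccoli, rocket, Granny Smith apple) was chosen to be disliked, and section 3.7.1 tells participants not to arrive very hungry. If about 1% would finish, the cap hardly matters. Willingness to eat the same salad twice in one session may also fall even when hunger has recovered, which leaves more headroom. Both points stand, and they are why the size is given as a range. They do not remove the point: the protocol cites no finishing rate, the portion is by its own account minimal, and the wait is extended until hunger returns to baseline.

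It is also fair that no directional hypothesis for intake is stated. The abstract speaks of change and the aims of comparison, so an expected increase is an inference from the introduction. Intake is one of several outcomes in these phases and is not designated primary. The taste and liking ratings have their own 0-100 scales, so the dose question does not rest on intake alone.

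Finally, details of a censored analysis could sit in an analysis plan that is not shown. But the portion is fixed here, and neither a linear model nor a GLMM for bounded data recovers desired intake above the served amount.

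**Conclusion.** The point holds conditionally. The cap is certain from the text, and a pre-test finisher cannot show an increase. Attenuation follows if MB raises desired intake and some participants reach the cap at either session. Its size runs from a few percent at 1% finishers to roughly half or more of the effect at 40% and above, under assumed normal desired intake, SDs of 25-50 g, shifts of 20-30 g and no drift.

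A reader might infer that the intake effect is bound to be materially biased towards zero. The documents do not support that: they give nothing from which the finishing rate can be judged, and the disliked salad makes a low rate plausible. A reader might also infer that a bigger portion is plainly the cure. Doubling it would restore 95-100% of the effect at 20-60% finishers in this model. With 1% finishers and s = 50 g, however, it moves the ratio only from 0.57-0.60 to 0.58-0.62, because the floor dominates. It would also add to the pre-test load in a single-session pre-post design.

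**What to change.** In Table 6, for intake:

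- Report by arm and session how many participants finish the portion, with finishing defined in advance by the leftover weight.
- Analyse intake with a mixed model that treats finished portions as right-censored at the weight served, at least as a sensitivity analysis beside the planned LMM/GLMM.
- State that a null or flat intake dose comparison will not be read as absence of effect, or as a plateau, where finishing is common.
- Apply this to Phase 3 as well. Tables 1 and 3 include intake there, but the Phase 3 rows of Table 6 do not list it.

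Served and leftover weights are already recorded, so the cost is analysis work. The drawback is that the censored model relies on a distributional assumption that 10 participants per arm can check only weakly, and it becomes fragile if most of an arm finishes.

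Where sessions are still to be run, the sponsor may consider a larger portion, identical at both sessions, with the minimum wait recalculated for its energy content. That has to be weighed against a greater pre-test load, possible carry-over of fullness and longer visits.

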### Data Collection Procedure

3.7

#### Standardization

3.7.1

For standardization, the following instructions will be sent to participants 24‐h prior to their scheduled visit (Phases 1–3). These procedures are intended to minimize variability in factors that may influence taste perception, food liking, appetite, and subsequent food intake.
Do not feel overly full or very hungry before attending the lab (Fu et al. 2021).Refrain from eating or drinking (except water) 1 h before attending the lab (McCrickerd et al. 2015).Do not brush your teeth 1 h before attending the lab (Choi and Garza 2020).Do not chew gum 1 h before attending the lab (Miquel‐Kergoat et al. 2015).Refrain from drinking alcohol for at least 8 h before attending the lab (Marinho Brazil et al. 2022).Do not smoke 1 h before attending the lab (Kale et al. 2019).Avoid strenuous physical activities 24 h before attending the lab (Douglas et al. 2017; Martins et al. 2015).Do not participate if you have experienced unexpected, sad/shocking, or happy events in the past 24 h. In such situations, participants will be allowed to book another day when their mood status returns to normal (Evers et al. 2018).

#### Phase 1

3.7.2

Food‐grade solutions representing each taste will be prepared, as outlined in Table 4. Upon arrival at the laboratory, participants will be asked to review the standardization instructions provided before their visit and confirm their adherence by ticking the relevant checklist.

**TABLE 4 fsn371640-tbl-0004:** Food‐grade solutions and food items with their concentrations and pH values representing each taste (Phase 1).

Taste type	Food‐grade solutions		Food items	
	Amount, concentration	pH	Amount	pH
Sour	10 mL solution of 10 mmol/L citric acid	2.60	Piece of lime (1/8th lime or ~12 g)	2.50
Bitter	10 mL of 3.2 mmol/L PROP	6.80	Broccoli floret (~20 g)	6.92
	5 mL of 10 mmol/L citric acid +5 mL of 3.2 mmol/L of PROP	2.70	5 mL of lime juice + Broccoli floret (~20 g)	4.00
Tart	10 mL of 7.5 mmol/L tartaric acid	3.78	Piece of Granny Smith apple without seeds (1/8th apple or ~18 g)	3.14
Sweet	10 mL of 96 mmol/L sucrose	7.00	5 mL maple syrup	6.78
	5 mL of 10 mmol/L citric acid +5 mL of 96 mmol/L sucrose	3.02	5 + 5 mL of lime juice + maple syrup	3.27

*Note:* For non‐acidic solutions and food items (bitter and tart), we planned to use the solutions mixed with citric acid, as an acidic pH was essential for the taste modification action of miraculin (Doddawad et al. 2022). Food samples were kept in a refrigerator, then removed and placed on separate plastic trays 10 min before each test.

First, sociodemographic characteristics and anthropometric measurements will be collected. Saliva samples will then be obtained for TAS2R38 genotyping, and oral pH and phenotypic taste sensitivity will be assessed. As illustrated in Figure 1, participants (*N* = 54) will subsequently be allocated into three groups (*n* = 18 per group). Prior to commencing the pre‐test session, participants will be instructed to drink a sip of water and wait at least 30 s (Choi and Garza 2020). In their respective groups, participants will receive 10 mL of each solution and pieces of single food items to rate their perceived taste perception on a generalized labeled magnitude scale (gLMS). Participants will rinse their mouths with water between each solution or food item until the previous taste stimulus is gone (Igarashi et al. 2013; Lipatova and Campolattaro 2016).

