 Daniell), a member of the Sapotaceae family (Misaka 2013). It comprises two glycosides attached to a single polypeptide chain with 191 amino acid residues (Kabore et al. 2022). Due to this active protein, MB has the unique ability to temporarily alter taste perception, making sour foods taste sweet (Diyapaththugama et al. 2024). This effect occurs from miraculin binding to taste receptors on the tongue and modifying how they respond to sour stimuli (Sanematsu et al. 2016). As a result, foods that are typically acidic (i.e., sour) can taste sweet after ingesting MB (Misaka 2013). Our previous review demonstrated that MB consistently decreases sourness and enhances sweetness in sour‐tasting solutions and food items. However, findings regarding its effects on bitter, salty, and sweet tastes remain inconsistent (Diyapaththugama et al. 2024). These discrepancies may stem from variations in experimental conditions, particularly considering that miraculin requires a pH range of 4.8–6.5 for activation (Akinmoladun et al. 2020; Doddawad et al. 2022).

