## Comments

4

Food liking results from a complex interplay of sensory perceptions, with taste playing a crucial role (Liem and Russell 2019). Humans have an innate preference for sweet tastes and an aversion to sour and bitter foods (Beauchamp 2016). Therefore, a practical approach to minimize sugar intake while maintaining food palatability is to provide alternative low‐calorie sweeteners (Arshad et al. 2022; Russell et al. 2021). As a potential low‐calorie sweetener, MB may alter the liking and subsequent consumption of hypo‐palatable foods (sour and bitter‐tasting fruits and vegetables) as well as hyper‐palatable foods and SSBs, potentially impacting overall dietary quality.

Several considerations should be acknowledged. Dietary data collected through self‐reported methods may be subject to recall bias, social desirability bias, and underreporting. To minimize these issues, mitigation strategies such as participant training, use of portion size estimation aids, and researcher probing will be applied during data collection. Nevertheless, the inherent limitations of self‐reported dietary methods highlight the need for cautious interpretation of the findings.

In conclusion, this project will generate new knowledge on the effects of different doses of MB on taste perception and preferences for hypo‐palatable foods and hyper‐palatable SSBs, while also providing evidence on the low‐pH requirement for its activation in both healthy‐weight and overweight/obese adults. Furthermore, it will examine the feasibility of using MB as a taste modifier to influence food preferences, energy intake, and dietary quality in a natural environment (i.e., at home). If MB demonstrates promising effects in this feasibility trial, larger‐scale studies in real‐life settings, including diverse population groups, will be needed to guide public health strategies for reducing added sugar consumption and promoting fruit and vegetable intake, which are key targets in dietary guidelines and chronic disease prevention efforts.

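### In Phase 1 the acidified bitter and sweet solutions hold half the tastant of the plain ones, so the low-pH claim is mixed with dilution; no overweight or obese adult is tested for it

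*Protocol article*

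**What the plan says.** Table 4 (section 3.7.2, Phase 1) lists four stimuli in both a plain and an acidified form:

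- Bitter solution: plain "10 mL of 3.2 mmol/L PROP" (pH 6.80); acidified "5 mL of 10 mmol/L citric acid +5 mL of 3.2 mmol/L of PROP" (pH 2.70).
- Sweet solution: plain "10 mL of 96 mmol/L sucrose" (pH 7.00); acidified "5 mL of 10 mmol/L citric acid +5 mL of 96 mmol/L sucrose" (pH 3.02).
- Bitter food: a broccoli floret of about 20 g (pH 6.92); acidified "5 mL of lime juice + Broccoli floret (~20 g") (pH 4.00).
- Sweet food: plain "5 mL maple syrup" (pH 6.78); acidified, 5 mL lime juice with 5 mL syrup (pH 3.27).

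The table note explains that acid is added because miraculin needs it to act. Section 3.7.2 has participants rate the same samples before and after the tablet. Table 6 analyses dose as a fixed effect and time as a within-subject factor, with pairwise comparisons between doses.

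The Comments (section 4) say that the project will deliver evidence on the low-pH "requirement for its activation in both" healthy-weight and overweight/obese adults. The Introduction says that "miraculin requires a pH range of" 4.8 to 6.5.

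**The concern.** To learn whether MB needs acid, one must compare its effect on a stimulus with acid and without it, all else equal. In the two solution pairs all else is not equal. The mixtures use stocks of the same strength as the plain samples, so adding acid also dilutes the tastant, and Table 4 lists no diluted sample without acid. A different MB effect in the two versions could come from acidity, from dilution or from both, because a weaker sample starts at a different rating and has different room to move on the 0–100 scale.

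The second problem is the population. The claim covers overweight and obese adults, but the phases that enrol them have no acid/plain contrast. What is at stake is one stated deliverable of the project, not its dose comparisons.

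**Working it through.** **Dilution.** The inputs are the volumes and concentrations in Table 4; section 3.7.2 confirms that 10 mL of each solution is served. Amount = volume × concentration. Final concentration = amount ÷ total volume, with total volume 5 + 5 = 10 mL, which reproduces the stated serving.

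- PROP, plain: 10 mL × 3.2 mmol/L = 32 µmol, at 3.2 mmol/L.
- PROP, acidified: 5 × 3.2 = 16 µmol; 16 ÷ 10 = 1.6 mmol/L. Ratio 0.50.
- Sucrose, plain: 10 × 96 = 960 µmol, at 96 mmol/L.
- Sucrose, acidified: 5 × 96 = 480 µmol; 480 ÷ 10 = 48 mmol/L. Ratio 0.50.
- Citric acid: 10 mmol/L in the sour solution; 5 × 10 ÷ 10 = 5 mmol/L in both mixtures.
- Maple syrup: 5 mL in both versions (amount ratio 1.0); 5 ÷ 10 = 0.5 of the concentration.
- Broccoli: about 20 g in both versions (ratio 1.0).

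So two of the four pairs halve both amount and concentration, one halves concentration only, and one halves neither.

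**What this could do to ratings.** The document gives no relation between concentration and rating. As an illustration only, assume that ratings follow a power function with exponent b. Halving the concentration then multiplies the pre-test rating by 0.5^b:

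- b = 0.5: 0.71
- b = 0.8: 0.57
- b = 1.0: 0.50
- b = 1.3: 0.41

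This shows how far the starting point might move. It does not estimate the bias in the MB effect.

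**Population.** Set against the claim in the Comments:

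- Phase 1 has the acid/plain pairs and enrols healthy-weight adults (section 2, Table 1).
- Phase 3 uses the same salad and cola procedure as Phase 2 (section 3.7.4), with no acid/plain pair.
- Phase 4 encourages lime with the tablets for all participants (section 3.7.5.2), so there is no comparison without it.
- Mouth pH is recorded in all phases (Table 3), but as an observed covariate, not as a manipulated condition.

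**pH wording.** Of the twelve pH values in Table 4, eight lie between 2.50 and 4.00 and four between 6.78 and 7.00. None lies between 4.8 and 6.5. The table note also names bitter and tart as the non-acidic items, whereas the table acidifies bitter and sweet and gives the tart items pH 3.78 and 3.14.

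**The case against.** The best defence is that no planned contrast is confounded. The Phase 1 objective concerns doses. Every dose group receives the same stimuli, and each stimulus is compared with itself before and after the tablet. Dilution is therefore constant within every pre-post and between-dose comparison. Table 6 names no acid-versus-plain contrast, and the table note presents the mixtures as a way to supply acid. This stands in full. A reader might infer that the dilution undermines the Phase 1 dose results; the documents do not support that. What the defence does not rescue is the claim in the Comments, which only an acid-versus-plain comparison could support.

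Three further points have weight. First, the direction differs by taste. A weaker bitter sample has less room to fall, so a larger bitter reduction with acid would appear despite the dilution. For sweetness, a lower start leaves more room to rise, so dilution could imitate the effect sought. Second, broccoli gives a pH contrast (6.92 against 4.00) at constant mass, so it goes too far to say that nothing can be learned about acid. Third, adding acid also adds a sour taste, which MB itself turns sweet. Even a strength-matched pair is therefore not a pure pH contrast.

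A reader might also infer from the 4.8–6.5 range that no Table 4 stimulus could activate miraculin. The Introduction does not say whether that range refers to the sample, the saliva or the receptor surface, so this is a wording query and not a demonstrated design fault.

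**Conclusion.** The point holds in a limited form. The acidified PROP and sucrose solutions contain exactly half the tastant of their plain counterparts, and the maple mixture has the same amount at half the concentration. It would be wrong to say that all acidified stimuli are halved, since broccoli is not.

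The dose and pre-post results stand. The comparison of MB effects between plain and acidified versions mixes acidity with tastant strength in the two solution pairs, and with concentration in the maple pair. The two-fold dilution is exact and needs no assumption. Its effect on the ratings cannot be computed, and the 0.71 to 0.41 range rests wholly on assumed exponents.

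Separately, and whatever is made of the dilution, the low-pH claim has no design support in overweight or obese adults.

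**What to change.** If Phase 1 can still be changed, match tastant strength within each solution pair by one of two routes:

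- Make the tastant stocks for the mixtures at double strength: 6.4 mmol/L PROP (5 × 6.4 ÷ 10 = 3.2) and 192 mmol/L sucrose (5 × 192 ÷ 10 = 96). If the acid is also to match the sour solution, use a 20 mmol/L citric acid stock (5 × 20 ÷ 10 = 10).
- Or keep the mixtures and use plain stock diluted 1:1 with water as the comparator (1.6 and 48 mmol/L).

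In either case bring the plain maple syrup to 10 mL with water. Describe the result as acidified versus plain, not as an effect of pH alone, because the acid brings its own taste. The cost is new recipes and re-measured pH values.

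Table 1 scheduled Phase 1 for July to September 2024, so it may already be complete. If so, state the confounding as a limitation and rest the acid/plain comparison mainly on the broccoli pair, which speaks only to bitterness.

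Whether or not Phase 1 has run, limit the low-pH statement in the Comments to healthy-weight adults. Say which pH the 4.8–6.5 range refers to and reconcile it with Table 4, and correct the table note so that it names the items actually acidified. These changes cost only wording.
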